## Abstract

**Background:**

Enteral nutrition is preferable over parenteral nutrition for critically ill patients, but is often discontinued due to enteral feeding intolerance. Diarrhea is one of the most common causes of the discontinuation of enteral nutrition and may be attributed to the composition of enteral formulas. Dietary fiber attenuates diarrhea by normalizing the intestinal microbiota, providing energy for colonic epithelial cells, and exerting a thickening effect on intestinal contents. We herein conducted a randomized controlled trial (RCT) to test the hypothesis that the administration of an enteral formula containing low-methoxy pectin, a type of dietary fiber, more effectively ameliorates diarrhea in critically ill adult patients than a similar composition without pectin.

**Methods:**

A protocol for planning a multicenter, parallel-group, open-label RCT is described herein. Enrolled patients are those ≥18 years of age with the indication of enteral nutrition by gastric access. Overall, 200 patients will be randomized into an intervention group administered an enteral formula containing low-methoxy pectin and a control group administered an enteral formula with similar components, but without pectin at a ratio of 1:1. Each enteral formula will be administered for 3 days or longer. There are no restrictions on other treatments. The primary outcome is the incidence of diarrhea as defined by Bristol Scale 5, 6, or 7. Secondary outcomes include the rate of EN failure, the survival rate, the lengths of ICU and hospital stays, and nutritional endpoints.

**Discussion:**

The present study examines the effects of a low-methoxy pectin-containing enteral formula on enteral feeding intolerance, including diarrhea, in critically ill patients. The results obtained may provide new considerations regarding the selection of enteral formulas for critically ill patients.

**Trial registration:**

jRCTs031230684 registered on 08 Mar 2024, https://jrct.niph.go.jp/en-latest-detail/jRCTs031230684.

## Introduction

### Background and rationale

Enteral nutrition (EN) may be preferable to parenteral nutrition (PN) as nutrition therapy for critically ill patients. The initiation of EN 24−48 hours after admission to the intensive care unit (ICU) has been shown to reduce infectious complications [1–3]. Based on these findings, international guidelines recommend early EN [4]. However, EN is often discontinued due to enteral feeding intolerance, including a large gastric residual volume, nausea, vomiting, constipation, and diarrhea [5]. Diarrhea occurs in 37.7–73.8% of critically ill patients and is one of the most common causes of the discontinuation of EN [6]. Therefore, the prevention and management of diarrhea are regarded as important issues for accomplishing nutrition therapy. The causes of diarrhea in critically ill patients vary widely and include the administration of broad spectrum antimicrobial agents, intestinal ischemia, and *Clostridium difficile* infection. If these causes are absent, diarrhea may be related to EN itself, including the composition of an enteral formula and the method of administration. A recent prospective cohort study identified EN (relative risk (RR) 1.23, 95% confidence interval (CI) 1.16-1.31) as the largest risk factor for diarrhea in ICU patients, followed by the duration of antimicrobial therapy (RR 1.02, 95% CI 1.02-1.03) and suppository use (RR 1.14, 95% CI 1.06-1.22) [6]. Several characteristics of enteral formulas have been associated with diarrhea, including high osmolarity, the amount of carbohydrates, fat, protein-based formulas, and no dietary fiber content.

Dietary fiber is an indigestible carbohydrate, and its fermentation by intestinal bacteria yields short-chain fatty acids, which provide energy for intestinal bacteria and colonic epithelial cells and also exert a thickening effect on intestinal contents, thereby attenuating diarrhea [7]. Pectin, a type of soluble dietary fiber, gelatinizes in an acidic environment, thereby delaying the arrival of gastric contents to the small intestine. In addition, a recent study using a rat model showed that low methoxy pectin, the degree of esterification of which is less than 50%, was particularly effective at regulating stool properties and suppressing diarrhea [8]. In our previous retrospective study, enteral formulas containing low methoxy pectin ameliorated diarrhea in ICU patients [9]. We herein hypothesized that the use of a low methoxy pectin-containing enteral formula suppresses diarrhea in critically ill patients, even that with high lipid and protein contents. We will conduct a multicenter randomized controlled trial (RCT) in which patients admitted to the ICU and indicated for EN are randomized into a low methoxy pectin-containing enteral formula group or control group.

## Trial registration

Trial identifier: jRCTs031230684. Registered on 08 Mar 2024.

Registry name: Low-Methoxy Pectin containing Enteral nutrition in Critically care for intestinal Tolerance (LOME-PECT trial)

### Protocol version

Ver. 2.0, updated on 18 June 2024. Copies of the protocol are shown in S2 File (English) and S3 File (Japanese).

### Role of the sponsor

The sponsor provides enteral formulas, but has no authority regarding the implementation of this study or data collection, its management, analysis, or interpretation. The joint clinical research agreement document is shown in S1 File.

### Objectives

The primary aim of this study is to examine the efficacy of an enteral formula containing low methoxy pectin against diarrhea in adult critically ill patients.

### Trial design

The LOME-PECT trial is a multicenter, parallel-group, open-label RCT. The study is Specified Clinical Research under the Clinical Trials Act in Japan. This clinical study will enroll 200 adult patients admitted to the ICU. The study period is between March 08th, 2024 and March 31st, 2028. The recruitment started on 26 June 2024 and will continue until 31 March 2025.

### Eligibility criteria

#### Inclusion criteria.

We include the following patients:

Admitted to the ICU (any reason for admission)Age ≥ 18 yearsIndication for EN by gastric feedingAgreeable to provide written informed consent for study participation.

#### Exclusion criteria.

We exclude the following patients:

Received enteral feeding within 30 days prior to enrollmentPresenting with diarrhea (Bristol scale ≥5) at enrollmentContraindications or medical inappropriateness (including allergies) to gastric feeding or enteral formulas“Do Not Resuscitate” policyReceived EN via gastrostoma or percutaneous trans-esophageal gastro-tubingJudged as inappropriate by a physician

### Who will take informed consent?

The principal investigator or sub-investigator at each site will obtain written consent for participation after confirming the eligibility of patients.

### Additional consent provisions for the collection and use of participant data and biological specimens in ancillary studies

Plasma, whole blood, and fecal samples will be optionally collected on Day 0 (before the initiation of EN), Day 3, and Day 7 for patients who have given their consent, and will be stored at −80°C. Samples will be anonymized at each institution and stored for a secondary analysis.

### Interventions

#### Explanation for the choice of comparators.

Patients in the control group will receive GLUCERNA® REX as the enteral formula. GLUCERNA® REX is a pectin-free enteral formula with a similar nutrient density and macronutrient balance to the test formula, HINEX® RENUTE.

#### Interventions for each group with sufficient detail to allow replication, including how and when they will be administered.

The SPIRIT Figure is shown in Fig 1 and the study outline is in Fig 2. After obtaining written consent from potentially eligible patients, the necessary tests will be conducted to confirm eligibility. The use of test data obtained before consent will be allowed. EN will be started at the discretion of the physician in charge according to medical indications. There is no time limit between enrollment and the initiation of EN, however, there are minimal practical barriers to starting EN in the enrolled patients, and efforts to align enrollment timing with EN initiation are encouraged in order to minimize cases where EN could not be commenced post-enrollment. Therefore, EN is expected to be initiated within 24 hours.

**Fig 1 pone.0326582.g001:**
[figure not shown]
The SPIRIT figure. Schedule of enrolment, interventions, and assessments. a: Dosing after Day 3 is allowed under clinical judgment. b: Only patients for whom additional consent was obtained. c: Bristol Scale ≥5, 200 g/day, or 300 ml/day.

**Fig 2 pone.0326582.g002:**
[figure not shown]
The study outline.

We adopt HINEX® RENUTE as the enteral formula in the intervention group because it contains low-methoxy pectin with an optimal composition for nutrition therapy for critically ill patients: low carbohydrate and high protein contents. In the control group, GLUCERNA® REX is used as the enteral formula with a similar lipid content and energy density (kcal/ml) to HINEX® RENUTE in terms of aligning the composition affecting diarrhea. HINEX® REUNUTE is a liquid nutrition formula that contains energy density 1.0 kcal/mL, collagen and soy peptide as the nitrogen source, osmotic pressure 380 mOsm/L, and a protein, fat, and carbohydrate balance of 24, 50, and 26%, respectively. It contains 0.68 g pectin per 100 kcal. GLUCERNA® REX is a liquid nutrition formula that contains energy density 1.0 kcal/mL, soy protein, osmotic pressure 560 mOsm/L, and a protein, fat, and carbohydrate balance of 17, 50, and 33%, respectively. It contains 0.9 g dietary fiber per 100 kcal. The treatment group will receive HINEX® RENUTE and the control group will receive GLUCERNA® REX by continuous gastric administration via a feeding tube for 3 days. At the physician’s discretion, any enteral formula may be administered until Day 7, except GLUCERNA® REX, in the treatment group and HINEX® RENUTE in the control group. After Day 8, neither the test nor control formula will be administered in both groups. The dose rate will start at 10 ml/h. If there are no adverse events, the dose rate will be increased by 10 ml/h every 8 hours. The target energy dose is not specified and may be selected by the physician, but will not exceed 20 kcal/kg until Day 3.

### Criteria for discontinuing or modifying allocated interventions

If a participant does not meet eligibility after enrollment and prior to administration of the study nutrient, the intervention will be terminated and no study nutrient will be administered.

### Strategies to improve adherence to interventions

Not applicable in the present study.

### Relevant concomitant care permitted or prohibited treatments during the trial

Enteral formulas other than the study nutrients will not be used in either group until the primary outcome is evaluated. However, non-nutritional medications may be administered, and PN may be used as appropriate. There are no restrictions on treatments other than nutrition therapy.

### Outcomes

#### Primary outcome.

The incidence of diarrhea (as defined by Bristol Scale 5, 6, or 7) within 3 days of the administration of study enteral formulas is evaluated as the primary outcome. Since the residence time of enteral formulas in the intestinal tract is approximately 24 hours and diarrhea, if accompanied, is expected to occur within the following 24 hours, it is considered sufficient to detect the onset of diarrhea within 3 days of starting EN. The Bristol Scale is applied as a measure of diarrhea, and a score of 5–7 is defined as diarrhea based on previous studies and a recent review [9–11].

#### Secondary outcomes.

Secondary outcomes are (1) the Bristol Scale, the presence or absence of diarrhea (≥200 g/day or 300 ml/day) and watery diarrhea (Bristol Scale 7) on Days 1, 2, and 3; (2) the occurrence of diarrhea (defined by Bristol Scale 5–7) in the first week; (3) the rate of EN failure on Days 3 and 7; (4) the duration of EN; (5) the daily doses of energy (kcal/day) and protein (g/day) for EN and PN during the first 7 days; (6) the survival rate on Day 28; (7) the length of ICU stay; (8) the length of hospital stay; (9) ventilator days; (10) nutritional endpoints: white blood cells, total lymphocyte count, C reactive protein, albumin, transthyretin, cholesterol (total, low density lipoprotein, and high density lipoprotein) and triglycerides on Days 7 and 14; (11) the Barthel index on Day 28; (12) the occurrence of adverse events, including enteral feeding intolerance and infectious complications.

### Participant timeline

The participant timeline is shown in Fig 2.

### Sample size

Based on our previous retrospective study, we estimated the incidence of diarrhea in this study [9]. The incidence of diarrhea in the control group using GLUCERNA® REX was estimated to be 50%, while that in the treatment group using HINEX® RENUTE was 30%. By applying Pearson’s chi-square test to the predicted incidence of diarrhea at a two-sided significance level of 5%, the number of cases required to maintain 80% power was calculated to be 93 in each group. In consideration of some dropouts, the target number of cases was set at 100 in each group, for a total of 200 cases.

### Recruitment

This study recruits patients for whom EN is indicated regardless of the reason for ICU admission; therefore, achieving the required number of participants is feasible.

### Assignment of interventions: allocation

#### Sequence generation and implementation.

Block randomization is performed using electronic data capture (EDC). The EDC site automatically generates a random sequence in each hospital; therefore, stratification is performed only for the facilities. Study physicians include participants on the EDC site, on which their allocation and assigned procedure are rapidly noted.

### Concealment mechanism

Researchers at one hospital are blinded to the assignments or outcomes of patients at other hospitals.

### Assignment of interventions: Blinding

#### Who will be blinded.

Difficulties are associated with blinding enteral formulas in this study due to hygiene concerns and potential clinical interference. Therefore, we planned this study as a non-blinded RCT. Trial participants, care providers, outcome assessors, and data analysts are not blinded. However, two or more ICU nurses who are not involved in this study assess diarrhea using the Bristol Scale, which they are familiar with in their clinical practice, and the secondary outcome, the amount of diarrhea, is an objective measure. Therefore, observer bias may be minimized.

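### Data analysts are left unblinded for a reason that applies only at the bedside, and the grounds given for limited observer bias do not protect the Bristol-based primary outcome

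*Protocol article*

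**What the plan says.** The section on who will be blinded gives one reason for the open-label design: "Difficulties are associated with blinding enteral formulas in this study due to hygiene concerns and potential clinical interference". It then declares: "Trial participants, care providers, outcome assessors, and data analysts are not blinded". No separate reason is given for the analysts.

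Two mitigations follow. The first is that "two or more ICU nurses who are not involved in this study assess diarrhea using the Bristol Scale". The second is that "the secondary outcome, the amount of diarrhea, is an objective measure". From these the article concludes: "Therefore, observer bias may be minimized".

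The main endpoint rests on the stool score alone and is worded thus: "The incidence of diarrhea (as defined by Bristol Scale 5, 6, or 7) within 3 days of the administration of study enteral formulas". By contrast, the weight or volume criterion (at least 200 g/day, or 300 ml/day) appears only under Secondary outcomes, for Days 1, 2 and 3.

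The statistical methods section defines the FAS as subjects without violations of the main eligibility criteria and without conflicts with the discontinuation and dropout criteria, and bases efficacy on it. It fixes Pearson's chi-square test, two-sided at 5%, without imputation, and announces a post-hoc subgroup analysis that follows from the results. The Confidentiality section gives the statistician access to all participants' data.

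**The concern.** There are two separate weaknesses.

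**Analysts.** A formula that cannot be masked at the bedside can still be analysed as arm A against arm B. The article makes an affirmative choice not to do so, and its stated reason does not cover that choice. The exposure lies in the FAS. Which eligibility violations count as main ones, and what counts as a dropout conflict, are judgements made after randomisation. If they are made with arms and outcomes in view, the primary comparison can move although the test itself is fixed.

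**Assessors.** The primary outcome turns on whether a stool is scored 4 or 5, by nurses whom the article itself lists as unblinded. An objective measure of a different outcome does not alter the error rate of the test on that score.

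**Working it through.** **1. The plan's own figure.** Inputs from Sample size: 50% against 30%, two-sided 5%, 80% power. With pooled variance and no continuity correction:

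n = [1.960·√(2·0.40·0.60) + 0.842·√(0.50·0.50 + 0.30·0.70)]² / 0.20² = 93 per group.

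This matches the article. Power at the target of 100 per group is 82.8%. No stated figure is in dispute.

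**2. The reason set against the choice.**

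| Unblinded role | Covered by hygiene or clinical interference? |
|---|---|
| Participants, care providers | Yes, these concern the feed itself |
| Outcome assessors at the bedside | Plausibly |
| Data analysts | No, a coded arm variable touches neither |

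**3. How far FAS decisions could reach.** The article gives no expected number of exclusions. It plans 100 per group against 93 required, an allowance of 7 per group. Assume, as an extreme, that all 7 are exclusions and that the true rate is 50% in both arms. Removing 7 diarrhoea cases from the test arm gives 43/93 = 46.2%. Removing 7 non-cases from the control arm gives 50/93 = 53.8%. The artificial gap is 7/93 = 7.5 points. This is a ceiling under that assumption, not an expected effect.

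**4. The two grounds for limited observer bias.**

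- Amount of diarrhoea: objective, but a secondary outcome. The primary definition uses the Bristol Scale alone, so this ground does not reach it.
- Two or more nurses outside the study: relevant to the Bristol score, and it removes a direct stake in the trial. But non-involvement is not masking, and the same section lists outcome assessors as unblinded.

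**5. What assessor bias could do (illustration).** Assumptions: no true difference, 100 per arm, Pearson chi-square at two-sided 5%, and test-arm incidence lowered by scoring alone. Exact binomial enumeration gives these rejection rates:

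| True rate in both arms | No shift | 5 points | 10 points |
|---|---|---|---|
| 50% | 5.6% | 11.8% | 31.0% |
| 30% | 5.1% | 12.4% | 37.1% |

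At 50%, rejections favouring the test formula go from 2.8% to 11.4% and 30.9%. Five points is a quarter of the planned 20-point effect. The shift sizes are assumed. The table describes mis-scoring by assessors and would be unchanged by coding the arms for the analyst.

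**6. Would coding hold?** Protein supplies 24% of energy in one formula and 17% in the other. At an assumed 4 kcal per gram, that is 24/4 = 6.0 g against 17/4 = 4.25 g per 100 kcal. Daily energy and protein are collected, so their ratio would reveal the arm unless withheld.

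**The case against.** The strongest replies are these.

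- **The primary test is fixed.** Pearson's test, two-sided 5%, no imputation and no interim analysis leave little for an analyst to choose, and a post-hoc subgroup cannot change the primary result. This stands, and it narrows the concern to FAS membership.
- **The analyst may not decide exclusions.** A reader might infer that the analyst applies the FAS exclusions and picks the subgroup. The article assigns neither task to anyone. What it supports is only that no step is stated to fix the FAS before arms are known.
- **The conclusion on bias is hedged.** A reader might take the article to claim that the objective secondary measure minimises bias in the primary outcome. It does not: it says only that bias may be minimised, names no outcome, and offers the outside nurses as well. The fault is that neither ground supports the reassurance where it is needed most.
- **Mis-scoring does not pass straight through.** A patient is a case if any stool within 3 days scores 5 to 7, so under-scoring removes a case only if every qualifying stool is under-scored. This stands, and is one reason to treat the table as illustrative.
- **Feeding discretion.** A reader might infer that unblinded physicians set exposure freely, since "The target energy dose is not specified and may be selected by the physician". The same paragraph caps energy at 20 kcal/kg until Day 3 and fixes the starting rate and increments. Without adverse events these give 8 × (10 + 20 + 30) = 480 ml in the first 24 hours in either arm. Daily enteral energy is already recorded and, at 1.0 kcal/mL for both formulas, gives delivered volume. Some discretion remains, but it needs no new data field.
- **Harder success rules.** One might require the weight or volume criterion and Bristol 7 to agree in direction with the primary result. Bristol 7 comes from the same unblinded raters, so it is no independent check. If 10% to 40% of diarrhoea cases met each criterion, equally across arms and independently (an assumption), power would fall from 83% to between about 45% and 77%. That cost is not justified here.

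**Conclusion.** The point holds as a cheap improvement, not as a flaw that undermines the trial. Open-label feeding is openly disclosed and not challenged. Leaving the analysts unblinded is a stated choice without a reason that fits it, and it matters because FAS exclusions after randomisation involve judgement. The size of that effect is unknown: the 7.5-point ceiling rests on treating the whole allowance of 7 per group as exclusions chosen in the worst direction.

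Separately, the reassurance on observer bias does not extend to the primary outcome. The rejection rates of 11.8% and 31.0% show what assumed assessor shifts of 5 and 10 points would do at a true 50%. A reader might take them as the cost of analyst unblinding, but they do not measure that.

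**What to change.** 1. **Code the arms.** Decide FAS membership and lock the primary analysis on data labelled A and B, prepared by someone other than the analyst. Withhold variables that reveal the arm, such as enteral protein, until lock. Cost: a coded export and a short delay in unmasking.
2. **Add an objective sensitivity analysis.** Pre-specify the criterion of at least 200 g/day or 300 ml/day on any of Days 1 to 3, by arm, as supportive of the primary result and not as a condition for success. Cost: analysis-plan wording only, since the daily data are already planned.
3. **Correct the blinding section.** Say that the nurses know the allocation, that the primary outcome remains open to observer bias, and that the objectivity argument applies only to the amount of diarrhoea.

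None of this changes patient care, data collection or the primary test. If the changes are made as a protocol modification, the article's own amendment route (review-board approval and patient consent) applies. Recruitment began on 26 June 2024, so they should be settled before anyone reviews outcomes by arm.

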### Data collection and management

#### Plans for the assessment and collection of outcomes.

The outcomes and baselines of all participants are collected and assessed on EDC. All data collection forms were newly created for use only in this study by TXP Medical Corp. Japan.

Baseline data to be collected consist of background characteristics, disease category, Sequential Organ Failure Assessment (SOFA), nutrition screening based on the Malnutrition Screening Tool (MUST), laboratory test, and gastrointestinal symptoms including Bristol scale [11–13]. Details of these items are shown in S1 Table. Descriptive statistics will be calculated to summarize these variables. Between-group inferential statistical comparisons will not be conducted, as these analyses are intended for descriptive purpose only.

